## Abstract

**Introduction:**

Seasonal (inactivated) influenza vaccination is recommended for all individuals aged 65+ and in individuals under 65 who are at an increased risk of complications of influenza infection, for example, people with asthma*.* Live attenuated influenza vaccine (LAIV) was recommended for children as they are thought to be responsible for much of the transmission of influenza to the populations at risk of serious complications from influenza. A phased roll-out of the LAIV pilot programme began in 2013/2014. There is limited evidence for vaccine effectiveness (VE) in the populations targeted for influenza vaccination. The aim of this study is to examine the safety and effectiveness of the live attenuated seasonal influenza vaccine programme in children and the inactivated seasonal influenza vaccination programme among different age and at-risk groups of people.

**Methods and analysis:**

Test negative and cohort study designs will be used to estimate VE. A primary care database covering 1.25 million people in Scotland for the period 2000/2001 to 2015/2016 will be linked to the Scottish Immunisation Recall Service (SIRS), Health Protection Scotland virology database, admissions to Scottish hospitals and the Scottish death register. Vaccination status (including LAIV uptake) will be determined from the primary care and SIRS database. The primary outcome will be influenza-positive real-time PCR tests carried out in sentinel general practices and other healthcare settings. Secondary outcomes include influenza-like illness and asthma-related general practice consultations, hospitalisations and death. An instrumental variable analysis will be carried out to account for confounding. Self-controlled study designs will be used to estimate the risk of adverse events associated with influenza vaccination.

**Ethics and dissemination:**

We obtained approval from the National Research Ethics Service Committee, West Midlands—Edgbaston. The study findings will be presented at international conferences and published in peer-reviewed journals.

**Trial registration number:**

ISRCTN88072400; Pre-results.

Strengths and limitations of this studyThe study population comprises a large, representative sample of the general population.We are developing a large national linked database, which contains anonymised individual patient-level data from general practices, hospitals, virology (real-time PCR) investigations and the death register.This is an observational study using routinely collected data, and therefore residual confounding may still be present or unaccounted for. We will measure the levels of unknown confounding required to impact on our study results.

## Introduction

Globally, it is estimated that seasonal influenza is responsible for five million cases of severe illness and 500 000 deaths per year, with an estimated cost to the USA of $87 billion per annum.^1^
^2^ Worldwide, there are an estimated 90 million new cases of influenza and 1 million cases of influenza-associated severe acute lower respiratory infection among children.^3^ National influenza vaccination programmes delivered by primary care in the community are important for reducing influenza-related illness, hence the considerable investment in this approach. These programmes previously targeted only older people (65+ years) and people considered at risk with chronic diseases, for example, asthma who are particularly susceptible to becoming seriously ill when they get influenza.

Children are important in the transmission of influenza to the populations at risk of serious complications from influenza and diminished circulation of virus has been predicted to improve herd immunity.^4^ Using evidence generated from epidemiological modelling,^5^ and following advice from the Joint Committee for Vaccination and Immunisation^6^ from September 2013, the seasonal influenza vaccination programme has been extended. In addition to the seasonal trivalent and quadrivalent inactivated influenza vaccine for at-risk individuals and those aged 65+ years, the live attenuated influenza vaccine (LAIV) is offered to all children aged 2–17 years (except those severely immunodeficient or those with severe asthma, prescribed immunosuppressive therapy or oral steroids) by primary care clinicians in general practice and schools in Scotland.

Clinical trials have found benefits of LAIV in healthy children under 7 years of age (most for under 3 years old).^7^
^8^ Efforts to estimate seasonal inactivated influenza vaccine effectiveness (VE) have been largely confined to younger, healthy adults (with few clinical trials showing efficacy in 65+ years and those with chronic disease).^9–11^ Recent observational studies have attempted to estimate the VE in preventing influenza-related illness in general practice patients.^12^ Further studies have examined VE with hospitalisation or death, however they have suffered from bias when using non-specific outcomes,^7^ or have been underpowered when using more specific end points such as laboratory-confirmed influenza, in particular for subgroups being targeted for vaccination (eg, 65+ years and people with at-risk disease such as asthma and pregnant women),^13^ cohort studies (with nested case–control studies) or data linkage-derived estimates of VE have been undertaken with measures taken to overcome many of the confounding issues that otherwise have limited estimations of effectiveness.^14–16^ There is also a need to add to the growing body of evidence with regard to the safety of these vaccines.^17^ Given the ongoing controversy regarding VE and in particular in relation to at-risk groups such as those with asthma,^7^ and the interim recommendation by the Advisory Committee on Immunization Practices (ACIP) not to use the LAIV in the USA during the 2016/2017 seasons,^18^ there is further need for information to help evaluate new policies regarding seasonal vaccine strategies.

This research aims to examine the VE and safety of the seasonal influenza vaccines including LAIV and the inactivated influenza vaccine. We will have access to a unique set of linked databases within a trusted research environment (TRE), which will contain individual patient-level data relating to primary healthcare, acute hospital care, school immunisation data, virological real-time PCR (RT-PCR) laboratory tests and mortality. In contrast to previous observational studies, these richer data sources will provide information on a large number of potential confounders and highly specific laboratory outcome measures in a study cohort sampled from the general population. Our assessment of the effectiveness and the public health impact of a new seasonal influenza vaccination programme seeks to clarify whether such a programme leads to societal benefits, therefore advancing the international evidence base. More specifically, the objectives of this study are to: (1) provide an estimate of the uptake and VE of LAIV administered to children (introduced to the national vaccination programme in 2013); (2) evaluate seasonal influenza VE in at-risk groups (eg, 65+ years, people with asthma, people with other comorbidities and pregnant women); and (3) measure adverse events associated with vaccination.

## Methods

### Study design and population

Vaccine uptake will be reported using serial cross-sectional surveys of each influenza season. The test-negative design (TND)^19^ will be used to measure VE for the RT-PCR outcomes and a cohort study design for non-specific clinical outcomes, for example, hospitalisation or death from influenza or pneumonia.

We will seek to extract data on up to 1.25 million people in Scotland by recruiting 220 general practices into our study. Each patient will contribute person-time to each influenza season while alive and registered with a participating general practice.

### Databases

Data fields extracted from the following databases will be linked deterministically using the Community Health Index (CHI) number—a unique identifier used by the National Health Service (NHS) for the Scottish population. The database linkage and analysis will occur within the National Services Scotland (NSS) TRE by the electronic Database Research and Innovation Service (eDRIS).

*General practice*: Almost all individuals resident in Scotland are registered with a general practice, which provides healthcare services free of charge. Virtually all specialist hospital care services are also free of charge, usually obtained through referral from primary care or, in emergency situations, through patients attending an accident and emergency department. Primary care-based physicians coordinate the influenza vaccination programme for their patients and provide much of the care of patients discharged back into the community by secondary and tertiary care services. Completeness of capture of contacts and accuracy of clinical event coding (using Read codes) has been found to be above 91% among practices in Scotland.^20^
^21^ The electronic recording of long-term prescribing information by primary care has also been found to be accurate and complete.^22^

*Scottish Immunisation Recall System*: The Scottish Immunisation Recall System (SIRS) is a database that has a record of all children (used nationally from 2002) with scheduled vaccinations. Data on vaccination administration for all children in Scotland are also recorded here.^23^ These data will be used to determine influenza vaccinations that have been administered in schools rather than in primary care.

*Electronic Communication of Surveillance in Scotland*: Data on more than 60 000 RT-PCR tests in total (including an additional 1500 tests per season funded to target 2-year and 3-year olds) have been collated into the Electronic Communication of Surveillance in Scotland (ECOSS) database which is used for the identification of severe disease, outbreaks and long-term trends in the incidence of laboratory-reported infections.^24^

*Scottish Morbidity Record*: The Information Services Division (ISD) maintains a database of all acute hospital discharges and deaths in Scotland, known as the Scottish Morbidity Record 1 (SMR01). All inpatient and day case episodes of care for acute hospitals since 1981 have been recorded in the database. The database is subject to regular validation checks, and the most recent quality assurance report indicated good levels of accuracy (>90%) for the fields used in this study.^25^ Diagnostic information is recorded using the International Classification of Disease V.10 (ICD-10). There are up to six fields the can be used to record diagnoses, with one allocated as the main reason for admission. SMR01 is linked routinely by ISD to the Scottish death register using patient characteristics in a probabilistic matching algorithm with a high degree of accuracy.^26^ Details from death certificates issued for all deaths in Scotland are recorded in the death register, maintained by National Records Scotland (NRS).^27^ Cause of death has been routinely coded using ICD-10 since 2000.

### Study period

Data from 1 September 2000 to 31 August 2016 will be used. This will allow analysis of 16 influenza seasons (2000/2001 to 2015/2016). Each patient will contribute person-time to each influenza season while alive and registered with a participating general practice. For the non-pandemic seasons, each year (1 September to 31 August) will be divided in to four periods (figure 1). The influenza season will be defined for each year using national influenza surveillance data.^28^ The other periods will include a preinfluenza season (starting 1 September), a postinfluenza period, which will end 31 May each year and a ‘non-influenza’ period from 1 June to 31 August (figure 1). In the prepandemic year 2008/2009, there will be no non-influenza period in the summer. The introduction of the influenza vaccination programme for children was phased over successive seasons. Therefore, in season 2013/2014 we will analyse data for children aged 2 and 3 years and those attending primary schools (where pilots were taking place) across Scotland; in seasons 2014/2015 and 2015/2016, we will analyse data for all preschool children aged 2–4 years and all primary school age children (ie, all children aged 2–11).

**Figure 1 BMJOPEN2016014200F1:**
[figure not shown]
Relationship of first influenza season (2000–2001) to preinfluenza, postinfluenza and non-influenza season periods. Baseline characteristics for each patient are determined on 1 September each year. The earliest date of influenza vaccination varied for each influenza season, but always occurred after 1 September.

### Exposure definition

For people in at-risk groups, influenza vaccinations (Trivalent Influenza Vaccine (TIV) and LAIV for preschool children aged ≥2 years) are free and administered by general practice.^29^ Data on influenza vaccination carried out in general practice (including CHI and date of administration) are recorded to enable reimbursement. Information on individuals receiving LAIV in schools is collated in the SIRS database and will be extracted for this analysis.^21^ Vaccination will be used to define exposure status if it is given at a time point between 1 September and the end of the influenza season (figure 1). An individual will be defined as vaccinated 14 days after the seasonal influenza vaccine has been administered.^30^ The time period from the first day of the influenza season to day 14 postvaccination will be defined as ‘unexposed’ and the period from day 14 postvaccination until the end of the influenza season will be defined as ‘exposed’. Therefore, those vaccinated between the start of the preinfluenza period up until 14 days before the influenza season will be defined as ‘exposed’ for the duration of the influenza season. We will exclude participants vaccinated <14 days prior to the RT-PCR test as a sensitivity analysis.

### Patient characteristics and confounding factors

Key characteristics of patients present in each season of the cohort will be included as confounders in the analyses. Confounders will be defined in each year on the first day of the preinfluenza season (1 September).

*Demographics*: Sex, age band and socioeconomic status will be included in all analyses; socioeconomic status will be measured using quintiles of the Scottish Index of Multiple Deprivation (SIMD). SIMD is an area-based measure of deprivation derived from seven domains including income, employment and education.^31^ Rurality in terms of urban/rural location (one large urban, six remote rural) will also be included in the analysis.

*At-risk groups*: At-risk patients are those with certain comorbidities for whom seasonal influenza vaccination is indicated. Patients will be defined as high risk according to national guidance^29^ if they have one or more of the following conditions:
Asthma;Chronic heart disease;Chronic kidney disease (including renal transplantation) stages 1–2 and 3–5;Chronic liver disease;Chronic neurological diseases;Chronic respiratory diseases;Conditions or drugs causing impaired immune function;Diabetes;Pregnancy (from 2009/2010);Asplenia or dysfunction of the spleen (from 2014/2015);Body mass index (for 2015/2016).

*Chronic diseases*: We will include this for our non-specific clinical outcomes and adverse events. Comorbidity will be defined by the 17 disease categories that constitute the Charlson Comorbidity Index.^32^ This Index has been validated in a number of different databases using codes from healthcare databases.^33^ Furthermore, a study has mapped Read codes from a UK general practice database to the relevant Charlson comorbid disease groups, resulting in a model that performed well in the prediction of 5-year mortality.^34^ These codes will be used to identify comorbidities that are present in a patent's record prior to the start of each preinfluenza season (1 September).

*Smoking status*: This will be derived from primary care data (current smoker, ex-smoker, non-smoker) and determined on 1 September each year.

*Previous vaccinations*: A variable will be included for patients who have received seasonal influenza vaccination in previous seasons to account for the possibility of persisting or reduced VE in the subsequent year.^35^
^36^ Adjustment for previous pneumococcal vaccination at any time in the primary care record prior to 1 September each year will also be undertaken.

*Previous healthcare usage*: Measures of previous healthcare resource use will also capture other aspects of chronic health status and include previous years general practitioner (GP) consultations, prescriptions (repeat) and number of admissions to hospital.

*Functional status*: There is no direct measure of functional status made in any of these national databases. However, individuals who are resident in some form of institutional care setting can be identified from the primary care database. This will also be used as an indicator of more severe functional limitation.

*Practice*: Accounting for the clustering of patients within GP practices, we will investigate whether practice characteristics (eg, training practice, list size, type of contract, etc) are associated with vaccine uptake.

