### Vaccine effectiveness

#### RT-PCR outcomes

For VE using information from linked virological RT-PCR swab data (a binary event) we will carry out a nested case test-negative control study.^19^ Influenza positivity will be compared with no influenza among patients who have ILI symptoms and tested for influenza. The primary analysis will be through a logistic generalised additive model where the effects of gender, age, socioeconomic status (SIMD^33^) and being in an at-risk morbidity group are adjusted for (a TND study). A spline function for time during each season will be included to model the background rate of influenza and correct for any potential bias associated with the proportions of test-negative and test-positive patients at different periods. VE will be measured by comparing the results from swabs taken after vaccination among those vaccinated to swabs taken among those unvaccinated at the time the swab is collected. Vaccination will be used to define exposure status if it was given at a time point between the 1 September and the end of the influenza season (figure 1). The adjusted estimate of VE=(1**−**OR)×100, where the OR is derived from the coefficient of vaccine status in the model. In our main analysis, we will assess only the first dose when two doses are given. We will carry out analysis stratified by influenza A (H1—including pandemic influenza and H3 subtype where recorded) and B.

We will carry out a number of sensitivity analyses for the primary end point:
*Non-sentinel* versus *sentinel*: We will explore the validity of using laboratory-confirmed influenza tests from non-sentinel primary care and secondary care sources versus sentinel primary care practices. Patient characteristics of individuals swabbed in non-sentinel primary care practices and secondary care will be described and any interaction between source of swab and outcome will be tested.*Negative controls*: As there should be no VE for influenza vaccine for these outcomes, we will explore the use of laboratory-confirmed infections (currently 10 respiratory viruses including rhinovirus and adenovirus) tested using multiplex RT-PCR at the same time as the influenza RT-PCR.*LAIV VE in younger/immunodeficient*: For younger vaccine-naïve or immunodeficient children receiving LAIV, we will account for any second dose in our model.

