#### Non-specific clinical outcomes

We will estimate VE for non-specific clinical outcomes: primary care consultations for ILI; all-cause emergency hospitalisation and death; and emergency hospitalisation and death due to influenza/pneumonia. Hospital admissions and consultations can have multiple events and each event will be counted.

For this proposal we have adopted methods we found in previous studies to be optimal for measuring VE and accounting for bias and confounding.^47^ Adjusted rate ratios of VE for prevention of hospitalisation/death/general practice consultation will be derived from time-dependent Cox models, taking into account the time at risk and the possibility of multiple events (not for death). Models will include a cluster term to account for intrapractice correlation. These models will adjust for gender, age, deprivation and clinical risk group and exposure to vaccination in each season included as a time-dependent covariate. Each season, individuals will begin in the unvaccinated group (and will accumulate time at risk) until 14 days after the receipt of the vaccine; then they will switch to the vaccinated group.

In all models used to estimate the VE, we will adjust for variables associated with the receipt of a vaccination and effect modifiers, such as vaccinations, consultations and hospitalisation in the previous influenza season, SIMD, urban/rural status, smoking status, Charlson score and pregnancy.

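### Pregnancy is fixed on 1 September with every other confounder, so many women pregnant during the influenza season are coded not pregnant, and many coded pregnant have delivered

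*Protocol article*

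**What the plan says.** Under Patient characteristics and confounding factors, the article sets one reference date for covariates: "Confounders will be defined in each year on the first day of the preinfluenza season (1 September"). The Figure 1 legend repeats it: "Baseline characteristics for each patient are determined on 1 September each year". The at-risk conditions under the first of these headings include "Pregnancy (from 2009/2010").

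Pregnancy then has three uses:

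- The second objective in the Introduction is to "evaluate seasonal influenza VE in at-risk groups (eg, 65+ years, people with asthma, people with other comorbidities and pregnant women").
- The primary RT-PCR model is one in which the effects of sex, age, deprivation and "being in an at-risk morbidity group are adjusted for".
- The closing paragraph of Non-specific clinical outcomes lists adjustment variables for all VE models, among them "urban/rural status, smoking status, Charlson score and pregnancy".

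The only covariate described as changing within a season is vaccination: "exposure to vaccination in each season included as a time-dependent covariate". The Figure 1 legend also says that the first vaccination date differs by season but never falls before the 1 September reference date.

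**The concern.** A yearly snapshot suits chronic conditions such as diabetes or chronic heart disease, which seldom change status over a winter. Pregnancy starts and ends within the study year and is itself an indication for vaccination. Two errors follow from a 1 September snapshot:

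- **Missed pregnancies.** Women who conceive after 1 September are coded not pregnant all season. Those vaccinated because of the pregnancy sit in the not-at-risk stratum unless they have another listed condition. This error is tied to exposure, because the uncoded pregnancy is the reason for the dose.
- **Ended pregnancies.** Women pregnant on 1 September who deliver before or during the season stay coded pregnant to its end.

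At stake is whether the estimate reported for pregnant women describes women who were pregnant when at risk of influenza, and whether adjusting for pregnancy removes confounding by indication among women of child-bearing age. The introduction itself names pregnant women among the subgroups for which earlier studies were underpowered, so losing eligible women from this group is costly.

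**Working it through.** The article gives no figure for pregnancy, so there is nothing to reproduce. The check asks how far a 1 September snapshot drifts from true status by the time of a swab or event.

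**Inputs from the article.** The snapshot is 1 September and vaccination comes after it. Pregnancy counts as an at-risk condition from 2009/2010, which is 7 of the 16 seasons. Season dates are set each year from national surveillance and no calendar dates are given. The post-influenza period ends on 31 May, so the season ends earlier.

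**Assumptions, not in the article.** Conceptions occur at a constant rate, pregnancy lasts L = 40 weeks (280 days) or 38 weeks (266 days), and pregnancy losses are ignored. Several season windows are tried.

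**Formula.** At d days after 1 September, time since conception among currently pregnant women is uniform on 0 to L. The share who conceived after the snapshot is d/L. Likewise, of women pregnant at the snapshot, the share who have since delivered is d/L. The two errors are therefore equal.

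| Date | d | d/280 | d/266 |
|---|---|---|---|
| 1 December | 91 | 33% | 34% |
| 15 December | 105 | 38% | 39% |
| 1 January | 122 | 44% | 46% |
| 1 February | 153 | 55% | 58% |
| 1 March | 181 | 65% | 68% |
| 31 March | 211 | 75% | 79% |

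Because the share is linear in d, its average over a window is its value at the midpoint:

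| Assumed season | Midpoint d | L = 280 | L = 266 |
|---|---|---|---|
| 1 Nov to 31 Dec | (61 + 121)/2 = 91 | 33% | 34% |
| 15 Dec to 28 Feb | (105 + 180)/2 = 142.5 | 51% | 54% |
| 1 Dec to 31 Mar | (91 + 211)/2 = 151 | 54% | 57% |
| 1 Oct to 17 May | (30 + 258)/2 = 144 | 51% | 54% |
| 1 Jan to 31 Mar | (122 + 211)/2 = 166.5 | 60% | 63% |

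**Recording delay.** Suppose pregnancy enters the record only from 6 weeks' gestation. Then, 20 weeks after the snapshot with L = 40 weeks, (20 + 6)/40 = 65% of currently pregnant women are coded not pregnant, and 20/(40 − 6) = 59% of those coded pregnant have delivered. With recording from 10 weeks, the figures are 30/40 = 75% and 20/30 = 67%.

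**After the change.** If pregnancy is dated at the swab or event, both timing errors are zero by construction, apart from recording delay and imprecise dates.

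**The case against.** The strongest reply is that no sentence dates pregnancy specifically. The 1 September date is restated for smoking, Charlson comorbidity and pneumococcal vaccination, but not in the at-risk paragraph, which refers to national guidance. How pregnancy episodes are dated could be left to a fuller document that is not shown. This lowers certainty about what the analysts will do, but not about what the article says. The lead-in sentence covers all confounders, the Figure 1 legend repeats it, and no exception is given. A fuller plan that dated pregnancy otherwise would conflict with the published rule.

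Four stronger readings are tempting and are not supported:

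- **That half are misclassified, as a fact.** This depends on season dates and a pregnancy length the article does not give. An early season gives about one third.
- **That the subgroup is largely the wrong women.** With L = 280, 56% of those coded pregnant are still pregnant on 1 January. Those who delivered in autumn may have been vaccinated while pregnant, so they are not simply wrong if the target is vaccine given in pregnancy. Missed conceptions are the more damaging error.
- **That VE is biased throughout.** No effect on a VE estimate has been calculated, and the article gives no number of pregnant women or of swabs from them. Two of the three groups with power calculations, children and people aged 65+, contain few or no pregnant women.
- **That uptake in pregnancy is certainly mis-stated.** The Vaccine uptake section neither names pregnancy nor restates a reference date. The error arises only if the general rule is applied there.

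**Conclusion.** The point holds as a defect in a stated rule. Read as written, the 1 September snapshot misclassifies pregnancy for a group named in the second objective and for a variable adjusted for in every VE model. Each error share averages roughly one third for an early season, 51–54% for mid-December to end February and about 60% for a late one. These figures rest on steady conceptions, a 38–40 week pregnancy, no losses and the assumed windows; delayed recording would raise them.

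The scope is limited to seasons from 2009/2010. The main casualties are VE in pregnant women and the pregnancy adjustment among women of child-bearing age. The effect on all-age, child and 65+ VE is probably small, although the article has no counts with which to show this. The point should be fixed, but it does not undermine the primary analysis as a whole.

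**What to change.** Add an explicit exception to the 1 September rule for pregnancy, and keep that date for chronic conditions:

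- **Test-negative analysis:** code pregnancy at the swab date.
- **Cox models:** code it as a time-dependent covariate from estimated conception to delivery. These models already carry vaccination in that form.
- **Uptake:** count women pregnant at any time in the vaccination period.

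Also state whether the target for pregnant women is VE while pregnant or VE of vaccine given in pregnancy. This decides how women who deliver between vaccination and swab are handled.

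Derive the dates from the primary care records. The hospital source described is acute inpatient and day-case data, and the article names no maternity dataset. The price is extra derivation work and some imprecision in estimated start and end dates, whose completeness should be checked first. No new contact with patients is needed.
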